#### Outcomes

*Primary outcome*
Improvements in self-reported sexual health from baseline to 6-month follow-up.*Secondary outcomes*Emotion regulation improvement (from baseline to 6-month follow-up).Reduction in automatic thoughts during sexual activity (from baseline to 6-month follow-up).Reduction in anxiety scores (from baseline to 6-month follow-up).Reduction in depression scores (from baseline to 6-month follow-up).Improvement in sexual self-schema (from baseline to 6-month follow-up).

### Measurements

Measurements will be undertaken at 3 time-points in each group: baseline, end of intervention, and 6-month follow up.

#### Sexual health

Sexual health will be assessed using four questionnaires, two of which concern self-perception as a sexual person, thoughts, and emotions during sexual activity and two questionnaires on sexual function.

Female participants will be asked to complete the Female Sexual Function Index (FSFI [27]) and the Sexual Quotient- female version (SQ-f [28]), while male participants will be asked to answer the International Index of Erectile Function (IIEF [29]) and the Sexual Quotient- male version (SQ-m [30]).

A) *Female Sexual Function Index (FSFI)* [27]: this is a 19-item questionnaire for the assessment of sexual functioning in women in domains of sexual functioning (e.g., sexual arousal, orgasm, satisfaction, pain). Answers are provided using a 5-point Likert scale. Hentschel et al. [31] translated and validated the he FSFI into Portuguese, showing good internal consistency both for the evaluation of the total scale (*α* = .92) and for specific domains (desire = .67; excitation = .80; lubrication = .89; orgasm = .87; satisfaction = .85; pain = .86).

B) *International Index of Erectile Function (IIEF)* [29]. The *IIEF* is 15-item, self-administered questionnaire for assessing sexual functioning in men. Answers are given on a 6-point Likert scale. The *IIEF* encompasses five different domains of sexual functioning: erectile function, orgasm function, sexual desire, intercourse satisfaction, and overall satisfaction. Ferraz and Cicconelli [32] translated and adapted the scale to Brazilian Portuguese. Its psychometric properties were assessed by Gonzáles et al. [33], showing good internal consistency for both the full scale (*α* = .89) and the specific domains (erectile function = .86; orgasmic function = .63; sexual desire = .77; sexual satisfaction = .60; general satisfaction = .73).

C) *Sexual Modes Questionnaire (SMQ)* – Automatic Thoughts subscale [34]. This self-report scale consists of 30 items in the male version and 33 items in the female version. Respondents are asked to rate the frequency (from 1 [never] to 5 [always]) with which they have experienced specific automatic thoughts during sexual activity. The psychometric properties of the Brazilian adapted version were evaluated by Lucena [35], with an internal consistency of *α* = .92 and retest reliability of *r* = .8 (*p* < .05) for the female version and *α* = .95 and *r* = .82 (*p* < .05) for internal consistency and reliability, respectively, for the male version.

D) *Sexual Quotient (QS)* [28, 30]. The *QS* is a brief and comprehensive tool composed of 10-questions, which are answered on a scale from 0 (never) to 5 (always). It addresses general sexual function and stages of the sexual response cycle (desire, arousal, orgasm) and sexual satisfaction. The female version showed excellent internal consistency, both for the questionnaire as a whole (*α* = .98) and for each of its domains (all with *α* ≥ .9) [28]. The male version showed satisfactory internal consistency for the questionnaire as a whole (*α* = .6) and for the separate domains (all with *α* ≥ .6).

E) *Sexual Self-Schema Scale (SSSS)*. Originally developed by Hill [36], the Brazilian version of the *SSSS* consists of 30 items assessing respondents’ perception of themselves as a sexual person compared to others of the same gender and age. Answers are provided using a 5-point Likert scale ranging from 1 (not at all descriptive of me) to 5 (very much descriptive of me). It has good test-retest reliability (*r* = .6, *p* < .05) and internal consistency (scale total Cronbach's alpha of .8, ranging from .61 to .85 for the three factors [35]).

#### Mental health assessment

for the assessment of mental health problems participants will complete the *Patient-Heath Questionnaire (PHQ-9)* and the *Generalized Anxiety Disorder 7* (*GAD-7)*. Both instruments are frequently used self-report diagnostic tools for the assessment of mental disorders.

a) The *Patient Health Questionnaire-9 (PHQ-9)* is a nine-item screening instrument, which also provides an assessment of the severity of depression. The diagnostic validity of the tool has been established for its English language version [37] as well as for the Brazilian version [38]. The questionnaire has good psychometric properties (77.5% sensitivity and 86.7% specificity) [39].

b) The *General Anxiety Disorder – 7 (GAD-7)* is a brief self-report measure specifically developed to assess Generalized Anxiety Disorder [40]. It has good reliability, as well as criterion, construct, factorial, and procedural validity. The Brazilian version has good internal consistency and reliability with Cronbach’s alpha of *α* = .916 and a rho composite reliability coefficient of *ρ* = .909 [41].

#### Emotion regulation assessment

For the assessment of emotion regulation, the *Difficulties in Emotion Regulation Scale (DERS)* will be used. The *DERS* is an empirically grounded assessment instrument measuring emotional regulation using a multidimensional framework, developed by Gratz and Roemer [42], and validated in Brazil by Miguel et al. [43] with its psychometric properties confirmed (*α* = .94 for the overall scale, ranging from 0.79 to 0.88 on subscales [44]). The *DERS* assesses several facets of emotion regulation, including difficulties relevant to an individual’s (a) acceptance of emotional responses, (b) ability to engage in goal-directed behavior under distress, (c) ability to control impulsive behaviors when distressed, (d) access to emotion regulation strategies, and (e) emotional clarity. Participants rate their degree of agreement with each statement on a scale from 1 (almost never; 0 to 10%) to 5 (almost always; 91 to 100%).

### Intervention

The intervention will involve an online emotion-regulation skills training for individuals with sexual problems. The protocol was developed based on existing emotion-regulation therapies [7, 10, 11, 45, 46]. It will last for 8 weeks, encompassing psycho-educational and emotion-regulation skills components. Every week participants will gain access to a different intervention module of the training, containing videos, presentation slides, written support material, and a recommendation of activities to be completed until the following week of training. Participants are expected to dedicate 30 min to 1 h per week to complete each module.

The intervention is structured as shown in Table 1.

**Table 1 Tab1:** Summary of intervention modules

	Module	Content
Week 1	Psycho-education on sexual function	Covers information about sexuality, sexual response cycle (desire, excitement, plateau, orgasm, resolution), and main difficulties that men and women may face in their sexual health, such as erectile dysfunction, premature ejaculation, desire disorders, pain disorders, and anorgasmia. It also differentiates the psychological characteristics of functional sexual response from a dysfunctional sexual response as well as the difference between sexual function and sexual satisfaction.
Week 2	Psycho-education on emotions and emotion regulation	Covers the definition of what emotions are, evolutionary aspects of emotions, emotion functions, emotion response cycles, emotion components (physical sensations, thoughts and behaviors), and long-term consequences of maintaining an emotional state for a longer period of time. It also defines pleasant and unpleasant emotions, the relationship between unpleasant emotion and avoidance behaviors, and avoidance strategies (emotional suppression, distraction and behavioral avoidance).
Week 3	Relaxation strategies: breathing and muscle relaxation	Informs about the common physiological response to anxiety and stress (e.g., increases in heart rate, respiration and muscle tension) and teaches two relaxation strategies: breathing relaxation and progressive muscle relaxation.
Week 4	Cognitive flexibility	Refers to the rational component of emotion regulation. Aims to conceptualize and enhance cognitive flexibility, the triad situation-thought-emotion is explained and detailed through the concepts of what distinguishes thoughts and interpretations, what automatic thoughts and cognitive distortions are, and the identification of negative thought patterns and most common cognitive distortions related to sexuality are described.
Week 5	Non-judgmental awareness	Aims at teaching participants to experience their emotions in the present moment in a nonjudgmental way. The module also differentiates between experiencing an unpleasant emotion from experiencing an unpleasant emotion resulting from negative beliefs and reactions to experiencing it (snowball effect).
Week 6	Self-acceptance and compassion	Focuses on two psychological concepts necessary for a better emotion management: acceptance and self-compassion. These are important in order not to avoid emotional experiences and to diminish self-criticism associated with sexual difficulties.
Week 7	Emotion analysis	Presents a step-by-step flow-chart of how to identify emotions when experiencing them. By identifying emotions properly, we facilitate effective emotion regulation. The flow chart is composed of 6 items to pay attention when identifying an emotion: (1) emotion, (2) event-trigger situation, (3) evaluation/interpretation, (4) physical sensations, (5) previous similar experiences, and (6) behavior.
Week 8	Sexual emotional exposures	Makes a summary of all previous modules and suggests a series of sexual experiences paying attention to the emotions experienced during the activities (exposures). Such gradual approach diminishes the risk of intense emotions and avoidant behaviors. By succeeding on the exposures, obtaining pleasure on the activities, assessments of danger/discomfort diminish and more adaptive evaluations arise, facilitating the identification and modification of emotional behaviors.

### Control

The control group will not receive any intervention during the trial but will be offered the same treatment at the end of the 6 months follow-up assessment (waitlist-control).

### Data collection and management

All necessary precautions will be taken to maintain the confidentiality of study participants. Information collected will be pseudonymized so that individual identities cannot be revealed. For each study participant, a unique identifier will be generated and associated with his/her data records. The identifier key list containing personal identifiers (name, address, phone number, etc.) will only be accessible to the investigators of the study. The key list will be stored in locked cabinet in the premises of the researcher’s institution (University of Luxembourg) and will be destroyed after the trial has come to an end.

The servers are located in a locked computer room where only authorized personnel form the University’s IT department have access using cards and keys. Sensitive data (contact information, journals, conversations, answers to assignments) will be stored encrypted in the database, using algorithms such as AES256 with secret keys etc.; furthermore, it is not possible to establish a link between this stored data and individual users by access to the database.

All data communication between servers and users is encrypted (via TLS/https). Each participant will be assigned a random user code (four digits followed by four letters), which is used by the researcher carrying out the intervention to identify participants during the intervention. All communication related to the treatment takes place on the platform, after logging in, like in bank systems, so no confidential information is sent unencrypted by e-mail. The software on the servers is kept up to date. Backup of data is taken regularly and will be kept in a separate location from the live servers. Consent forms will contain participant’s signature and his/her unique identification number.

The controlled access to the intervention platform will guarantee the confidentiality of personal identity and the right to the protection of personal data and privacy of individuals involved in the data collection. The integrity of the study will be monitored by the Thesis Supervision Committee under which the study is being conducted.

Study results will be presented as aggregated data, with no personal information. No reference to individual participants will be made in a way that allows for identification.

### Data analysis

Data will be analyzed based on three measurements: baseline, end of intervention, and follow-up 6 months later. Analyses will be conducted to ascertain the balance on the measured covariates between the treatment and the control group.

To avoid potential post-treatment complications, such as noncompliance behavior after treatment assignment, the standard intention-to-treat estimate will be performed. To assess mean differences in the different domains (sexual health, emotion regulation, mental health, and sexual self-perception) over time and between groups, repeated-measures analysis of variance will be performed, with time (assessment point) as the within-subject factor, and intervention (group) as the between-subject factor. In case of violation of normality, changes over time in groups will be assessed with related-samples Wilcoxon tests. Multiple-imputation-based methods will be used to address missing data at follow-ups.

Intervention adherence will be monitored by the number of participants accessing the weekly training modules.

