## Methods

### Design

A randomized controlled trial will be conducted. Participants will be allocated to either group 1 (intervention) or group 2 (waitlist).

Randomization will be performed prior to the enrolment of study participants. Two separate block randomization lists will be created (one per sex) via sealed envelope and participants with baseline completed will be allocated either on the TREPS intervention group or to a waitlist control group. The allocation will be conducted by a clinical psychologist with no involvement in the project and the intervention provider will have no influence on participants allocation. Analyses will be conducted and presented following the Consolidated Standards of Reporting Trials (CONSORT) statement [24, 25].

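### Baseline is analysed as an outcome level instead of a covariate, and the balance check has no stated consequence; the 5% level holds, but precision is lost and post hoc covariate choice is left open

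*Protocol article*

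**What the plan says.** All statements are in the protocol article.

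- **Balance check** (Data analysis): "Analyses will be conducted to ascertain the balance on the measured covariates between the treatment and the control group". The method, the covariates meant and the consequence are not given.
- **Model** (Data analysis): "repeated-measures analysis of variance will be performed, with time (assessment point) as the within-subject factor, and intervention (group) as the between-subject factor". No covariate is named.
- **Role of baseline** (Data analysis): "Data will be analyzed based on three measurements: baseline, end of intervention, and follow-up 6 months later". Baseline is therefore a level of the within-subject factor.
- **Fallback** (Data analysis): "In case of violation of normality, changes over time in groups will be assessed with related-samples Wilcoxon tests". This does not adjust for baseline either.
- **Primary outcome** (Outcomes): "Improvements in self-reported sexual health from baseline to 6-month follow-up".
- **Timing** (Design): "participants with baseline completed will be allocated either on the TREPS intervention group or to a waitlist control group". Baseline scores thus exist for everyone before allocation. The randomisation lists are separate by sex only, so baseline severity is balanced by chance alone.

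**The concern.** Because allocation is random and follows the baseline assessment, any baseline difference between arms is due to chance. Checking for balance then answers no inferential question. It matters only if it changes the analysis, and the plan does not say whether it may.

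The model also makes poor use of the baseline score. With baseline among the repeated outcomes, the group-by-time contrast subtracts the whole baseline difference. Only a fraction rho of that difference is expected to persist to follow-up, so subtracting all of it over-corrects. An arm that starts worse by chance then appears to improve more.

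Two things are at stake: precision, which is lost in every trial, balanced or not; and freedom to choose covariates once an imbalance has been seen.

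**Working it through.** **Inputs.** The Sample size section gives 51 per arm (102 in total, or 102 per gender if the target of 204 is met). The documents give no SD, no correlation between visits and no effect size. Assumed here: SD 1 at every visit, equal correlation rho of 0.3 to 0.7 between visits, no dropout. The plan states no figure on this point that could be reproduced.

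**1. Precision.** Per participant, the change score has variance 2(1-rho). The follow-up score adjusted for baseline has variance 1-rho². The ratio is (1-rho²)/[2(1-rho)] = (1+rho)/2.

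| rho | adjusted / change variance | equivalent n per arm for 51 |
|---|---|---|
| 0.3 | 0.65 | 0.65 × 51 = 33.2 |
| 0.5 | 0.75 | 0.75 × 51 = 38.3 |
| 0.7 | 0.85 | 0.85 × 51 = 43.4 |

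The last column is the size at which an adjusted comparison matches the change comparison with 51 per arm.

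**2. Power.** Simulated with 10,000 trials per setting, 51 per arm, three visits and an assumed effect of 0.5 SD at both post-baseline visits:

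| rho | baseline-adjusted, last visit | group-by-time test | change-score t-test |
|---|---|---|---|
| 0.5 | 82% | 73% | 70% |
| 0.7 | 93% | 92% | 89% |

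The gain over the planned interaction test is material at rho 0.5 and small at rho 0.7.

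**3. Overall type I error.** In the same simulations with no effect, the group-by-time test rejected in 5.1% of trials at both rho 0.5 and rho 0.7. A separate set of 40,000 null trials per setting gave 5.0%, 4.9% and 5.1% at rho 0.3, 0.5 and 0.7. The level is kept.

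**4. Bias given a baseline difference D.** The expected follow-up difference is rho·D, so the expected difference in change is rho·D - D = -(1-rho)D. The standard error of a chance baseline difference is sqrt(2/51) = 0.198 SD.

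| rho | bias at D = 1 SE (0.198 SD) | bias at D = 1.96 SE (0.388 SD) |
|---|---|---|
| 0.3 | 0.139 SD | 0.272 SD |
| 0.5 | 0.099 SD | 0.194 SD |
| 0.7 | 0.059 SD | 0.116 SD |

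**5. Error rate of the change contrast given D.** Conditionally, it has mean -(1-rho)D and SD sqrt(1-rho²) × 0.198, and is compared with 1.96 × sqrt(2(1-rho)) × 0.198. For rho 0.5 and D at 1.96 SE, the mean is 0.194, the SD 0.866 × 0.198 = 0.171 and the critical value 0.388. The rejection probability is 12.9%. For rho 0.3 and 0.7 it is 16.0% and 9.8%. At D of 1 SE it stays at 4.6% to 5.0%.

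In the null trials of step 2 with an imbalance beyond 1.96 SE, the group-by-time test rejected in 15% (rho 0.5) and 13% (rho 0.7). The baseline-adjusted comparison rejected in 5.0% at both. About 5% of trials per score fall in this group.

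**The case against.** The strongest reply is that repeated-measures ANOVA is a valid analysis of a randomised trial, and that a condensed article may leave covariates and the handling of imbalance to an analysis plan that is not shown. The first part stands. The second stands only in part: the article does more than omit a covariate list, because it assigns baseline to the outcome levels. A later plan that adjusted for baseline would have to change that stated model.

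Four stronger readings are tempting, and the documents do not support them.

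- *The planned test has an inflated false-positive rate.* It does not. The higher rates in step 5 hold only for trials selected for a marked imbalance. At rho 0.5, such an imbalance and a false positive occur together in roughly 0.05 × 0.155 = 0.8% of null trials (0.155 is the rate in the 40,000-trial set given a baseline difference at p < .05). Lower rates in the other trials offset this.
- *The model leaves imbalance uncorrected.* For the outcome's own baseline it over-corrects. The word fits only other prognostic covariates.
- *The balance check is a set of significance tests that will throw up false alarms.* The article does not say so, nor that the covariates are the outcome scales. Since the Design section commits to CONSORT reporting, the sentence may mean no more than a descriptive table.
- *The plan intends data-driven adjustment.* None is announced. The text merely does not exclude it.

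**Conclusion.** The point holds as one of efficiency and prespecification; the planned test is not invalid. The article fixes a model that treats baseline as an outcome, and pairs it with a balance check that has no stated use. The unconditional cost is precision: prespecified adjustment would bring the variance of the last-visit comparison to 0.65 to 0.85 of the change-score variance for rho 0.3 to 0.7. The conditional cost is a bias of about -(1-rho)D towards the arm that starts worse, for example 0.19 SD at rho 0.5 with a baseline difference of 1.96 SE.

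These sizes rest on the assumed rho, equal SDs and equal correlations. The eligibility cut-offs restrict the baseline range of the FSFI and IIEF, so equal SDs are only an approximation for those scales. The bias in SD units also depends on the numbers analysed: for a scale pooled over both sexes at 102 per arm, the standard error of a chance difference is sqrt(2/102) = 0.140 SD instead of 0.198. The variance ratio does not depend on the sample size.

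**What to change.** Change two sentences in the Data analysis section.

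1. Replace the balance sentence with: *Baseline characteristics will be tabulated descriptively by arm and sex. No covariate will be added or dropped because of observed baseline differences.*
2. Amend the ANOVA sentence so that baseline is no longer an outcome level: *The scores at the two post-baseline assessments are the outcomes. They will be compared between arms with the baseline score of the same outcome as a prespecified covariate, and with sex, the randomisation stratum, as a further covariate where both sexes are pooled, whatever the observed balance.*

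Both changes are needed together. Adding the baseline covariate while leaving baseline among the repeated levels would make it outcome and covariate at once. The Wilcoxon fallback should be checked against the amended model, since within-group paired tests give no adjusted comparison between arms.

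Cost: one or two degrees of freedom per model, and no new data, because baseline is complete before allocation.

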### Sample size

Considering the number of variables of the study (with a power of .80 or greater and with a significance level set at *α* = .05), the minimum sample size needed to find meaningful differences in sexual health is 102 participants (51 in the intervention and 51 the control group [26]). Considering gender differences, we will aim to obtain twice this sample size (*N* = 204), i.e., 102 participants per gender.

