12. Intervention(s)	*Emotion regulation skills training*: The intervention will consist in an online emotion-regulation skills training for individuals with sexual problems. It will last for 8 weeks, encompassing psycho-educational and emotion-regulation skills components. Every week participants will gain access to a different intervention module of the training, containing videos, presentation slides, written support material, and a recommendation of activities to be completed until the following week of training. Participants are expected to dedicate 30 min to 1 h per week to complete each module.
13. Key inclusion and exclusion criteria	*Inclusion criteria for participants:* 1. Between 18 and 65 years of age. 2. Fluent in Brazilian Portuguese. 3. Self-reported sexual problems, assessed in men by a score of < 21 on the International Index Erectile Function (IIEF) and in women by a score of < 26 on the Female Sexual Function Index (FSFI). 4. In a stable relationship for at least the preceding 3 months. *Exclusion criteria for participants:* 1. Medical conditions that can interfere with the outcomes of the intervention, e.g., diabetes, cancer, and cardiovascular problems. 2. Ongoing psychotherapy.
14. Study type	Type: interventional Study design: - Allocation: randomized. - Intervention model: parallel assignment. - Masking: none (open label) - Primary purpose: treatment
15. Date of first enrolment	10 March 2021
16. Sample size	102
17. Recruitment status	Enrolling
18. Primary outcome(s)	- Change in Female Sexual Function Index (FSFI) at 6 months (time frame: baseline, 2 months after baseline (end of intervention), and 8 months after baseline (follow-up)). - Change in International Index of Erectile Function (IIEF) at 6 months (time frame: baseline, 2 months after baseline (end of intervention), and 8 months after baseline (follow-up)). - Change in Sexual Quotient (QS) at 6 months (time frame: baseline, 2 months after baseline (end of intervention), and 8 months after baseline (follow-up)).

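### The named repeated-measures ANOVA is not tied to the 6-month follow-up that defines the primary outcome, so an effect present only at end of intervention could be read as primary success

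*Protocol article*

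**What the plan says.** In the protocol article, the Outcomes section gives the primary outcome as "Improvements in self-reported sexual health from baseline to 6-month follow-up". Table 2, item 18 (under Ethics approval), lists the primary measures as FSFI, IIEF and Sexual Quotient (QS). Each is a change at 6 months with all three visits in the time frame, for example "Change in Female Sexual Function Index (FSFI) at 6 months (time frame: baseline, 2 months after baseline (end of intervention), and 8 months after baseline".

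The Data analysis section opens with "Data will be analyzed based on three measurements: baseline, end of intervention, and follow-up 6 months later". For every domain alike it then plans one analysis: "repeated-measures analysis of variance will be performed, with time (assessment point) as the within-subject factor, and intervention (group) as the between-subject factor". It names no interaction term, no baseline-to-follow-up contrast and no deciding visit. The fallback is "In case of violation of normality, changes over time in groups will be assessed with related-samples Wilcoxon tests".

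The Sample size section gives 51 per arm "with a power of .80 or greater" and alpha .05. The target is 102 per gender, so 51 per arm within each gender. It states no effect size, sidedness, test or correlation between visits.

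**The concern.** The endpoint is a comparison at one visit, and the named analysis is a model over three. Two tests between arms come out of such a model by default:

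- The group-by-time test (2 df) asks whether the arms' profiles over the three visits are parallel. A difference at end of intervention alone is enough to make it significant.
- The group main effect averages the arm difference over all three visits. One of these is baseline, where randomisation rules out a treatment effect.

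Neither is the change to follow-up. The Wilcoxon fallback does not close the gap, because related-samples tests within groups do not compare the arms.

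Persistence matters in this trial. The article lists the 6-month assessment among its strengths, and the waitlist arm stays untreated until after it. The trial is also open label. If no deciding contrast is fixed, an effect that appears at week 8 and then fades could be presented as success on the 6-month outcome.

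**Working it through.** **The plan's own figure.** The 102 cannot be reproduced, because no effect size or test is given. By t test, d = 0.5 needs 51 per arm one-sided and 64 two-sided; a two-sided test with d of about 0.56 also comes close to 51. Several assumptions fit, so 102 is not shown to be wrong. It is used here only as an input.

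**Inputs.** From the article: n = 51 per arm, alpha 0.05, three visits. Assumed: two-sided test, SD 1 at each visit, equal correlation ρ = 0.3, 0.5 or 0.7 between visits, complete data, one outcome. Arm differences at the three visits are δ = (0, δ₁, δ₂), with mean δ̄.

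**Noncentrality (λ) of each test.**
- Group-by-time, F(2, 200): λ = n Σ(δₜ − δ̄)² / [2(1 − ρ)]
- Group main effect, F(1, 100): λ = n δ̄² / [2(1 + 2ρ)/3]
- Unadjusted change to follow-up, F(1, 100): λ = n δ₂² / [4(1 − ρ)]
- ANCOVA at follow-up with baseline as covariate, F(1, 99): λ = n δ₂² / [2(1 − ρ²)]

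**Effect at end of intervention only.** Take δ = (0, 0.5, 0) and ρ = 0.5. Then Σ(δₜ − δ̄)² = 0.25 − 0.25/3 = 0.1667, and λ = 51 × 0.1667 / 1 = 8.5, so the interaction is significant in 74% of trials. For the change contrast and ANCOVA λ = 0, so they reject in 5%.

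| δ₁, with δ₂ = 0 | Interaction significant, ρ = 0.3 / 0.5 / 0.7 | Follow-up contrast |
|---|---|---|
| 0.3 | 24 / 32 / 51% | 5% |
| 0.5 | 58 / 74 / 93% | 5% |
| 0.6 | 75 / 88 / 99% | 5% |

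For δ₁ = 0.5 the group main effect rejects in 21 / 18 / 15%. Simulation (20,000 runs) gave the same interaction rates for 0.5, and 56 / 71 / 92% under first-order autoregressive correlation, so the result does not depend on equal correlations.

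**Sustained effect.** Take δ = (0, 0.5, 0.5) and ρ = 0.5.
- Interaction: Σ(δₜ − δ̄)² = 0.5 − 1/3 = 0.1667, so λ is again 8.5. Under equal correlations the interaction test gives the same result whether the effect lasts or vanishes.
- Main effect: λ = 51 × 0.1111 / 1.333 = 4.25.
- Change: λ = 51 × 0.25 / 2 = 6.375.
- ANCOVA: λ = 51 × 0.25 / 1.5 = 8.5, on 1 df.

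| Test | Power, ρ = 0.3 / 0.5 / 0.7 |
|---|---|
| ANCOVA at follow-up | 75 / 82 / 94% |
| Interaction | 58 / 74 / 93% |
| Unadjusted change | 56 / 71 / 90% |
| Group main effect | 63 / 53 / 46% |

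At ρ = 0.8 the interaction and ANCOVA are level (both about 99%).

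**Other patterns at ρ = 0.5.** For a fading effect (0.5 then 0.25): interaction 61%, ANCOVA 30%, change 24%. For a building effect (0.25 then 0.5): interaction 61%, change 71%, ANCOVA 82%.

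**The case against.** The strongest reply is that the article names a model, not a deciding test. A baseline-to-follow-up contrast between arms is a standard 1-df contrast within that model, and an analysis plan that is not shown may specify it. This stands against the inference that the planned model cannot test the endpoint: it can. It does not remove the point that the article fixes both an endpoint and an analysis and leaves them unconnected.

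A reader might also infer that the ANOVA generally loses power. The figures do not support that. For a sustained effect the interaction is slightly stronger than the unadjusted change contrast, and for a fading one it is much stronger. It loses to ANCOVA for a sustained effect, by 17 / 9 / 1 points at ρ = 0.3 / 0.5 / 0.7, and the loss vanishes near 0.8. The group main effect does lose heavily, but the article never says that it decides.

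A third tempting reading is that Table 2 contradicts itself with "Change in Female Sexual Function Index (FSFI) at 6 months". The same entry places follow-up 8 months after baseline, and 2 months of intervention plus 6 months gives 8. The label is loose, but the timing is clear.

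Finally, treating baseline as a level of the outcome is a legitimate analysis of a randomised trial, and the univariate ANOVA needs sphericity, which is weaker than equal correlations. Neither choice is an error in itself.

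**Conclusion.** The point holds as a mismatch between endpoint and named analysis. Success on change to follow-up could be declared from an omnibus test that an end-of-intervention effect alone makes significant in roughly a quarter to nearly all trials (24% to 99% over 0.3 to 0.6 SD and ρ of 0.3 to 0.7), where a follow-up contrast would reject in 5%. These rates rest on assumed effect sizes and correlations, an effect that vanishes completely, complete data and a single outcome. The direction of the problem does not depend on them; the size does.

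Power is a secondary argument. It favours a baseline-adjusted follow-up contrast over the interaction at low to moderate correlation when the effect lasts, and no more than that. The documents do not support saying that the model is incapable of testing the endpoint or that the follow-up date is wrong.

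**What to change.** For each primary measure (FSFI in women, IIEF in men, QS), state that the primary test is the baseline-adjusted difference between arms at the follow-up visit, 8 months after baseline. Two routes would serve:

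- ANCOVA of the follow-up score on arm and baseline score, within the multiple imputation already planned; or
- a mixed model of the 2- and 8-month scores with arm, visit, arm-by-visit and baseline score as covariate, and unstructured covariance, reading off the arm difference at 8 months.

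Make the end-of-intervention contrast secondary and keep the repeated-measures ANOVA as supportive only. Any fallback for non-normal scores should likewise compare the arms at follow-up. It would help to describe the Table 2 visit as 8 months after baseline throughout.

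The cost is analysis wording, since the baseline scores and visits are already scheduled, and it is best settled before outcomes are seen by arm. There is a real trade-off: a follow-up test is less likely to detect an effect that fades (30% against 61% for the interaction, for 0.5 then 0.25 SD at ρ = 0.5). That is acceptable because follow-up is the endpoint the trial has chosen, and the secondary contrast still reports the early effect.
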